## Abstract

**Background:**

In an attempt to deal with the pressures on the health-care system and to guarantee sustainability, changes are needed. This study focuses on a cardiology primary care plus intervention. Primary care plus (PC+) is a new health-care delivery model focused on substitution of specialist care in the hospital setting with specialist care in the primary care setting. The intervention consists of a cardiology PC+ centre in which cardiologists, supported by other health-care professionals, provide consultations in a primary care setting. The PC+ centre aims to improve the health of the population and quality of care as experienced by patients, and reduce the number of referrals to hospital-based outpatient specialist care in order to reduce health-care costs. These aims reflect the Triple Aim principle. Hence, the objectives of the study are to evaluate the cardiology PC+ centre in terms of the Triple Aim outcomes and to evaluate the process of the introduction of PC+.

**Methods/Design:**

The study is a practice-based, quantitative study with a longitudinal observational design, and an additional qualitative study to supplement, interpret and improve the quantitative study. The study population of the quantitative part will consist of adult patients (≥18 years) with non-acute and low-complexity cardiology-related health complaints, who will be referred to the cardiology PC+ centre (intervention group) or hospital-based outpatient cardiology care (control group). All eligible patients will be asked to complete questionnaires at three different time points consisting of questions about their demographics, health status and experience of care. Additionally, quantitative data will be collected about health-care utilization and related health-care costs at the PC+ centre and the hospital. The qualitative part, consisting of semi-structured interviews, focus groups, and observations, is designed to evaluate the process as well as to amplify, clarify and explain quantitative results.

**Conclusions:**

This study will evaluate a cardiology PC+ centre using quantitative and supplementary qualitative methods. The findings of both sub-studies will fill a gap in knowledge about the effects of PC+ and in particular whether PC+ is able to pursue the Triple Aim outcomes.

**Trial registration:**

NTR6629 (Data registered: 25-08-2017) (registered retrospectively).

**Electronic supplementary material:**

The online version of this article (10.1186/s12913-017-2580-x) contains supplementary material, which is available to authorized users.

## Background

In an attempt to deal with the pressures on the health-care system and to guarantee sustainability, changes are needed [1, 2]. The aging population, along with an increase in chronically ill patients and medical and technological developments are expected to cause an even further increase in the health-care expenditures in most Western countries [3–5]. To guarantee sustainability, the health-care system should focus on high-value health care. This implies that initiatives should focus on simultaneously pursuing the three aims: improving the health of the population, improving the quality of care (as experienced by patients) and reducing the increase of health-care costs. This is known as the ‘Triple Aim’ principle of Berwick and colleagues [6, 7].

During the past few years, the Dutch Ministry of Health has determined strategies to limit the growth of health-care costs and to increase quality of care [2, 8–12]. A concrete action in line with these strategies includes that the Ministry of Health appointed nine regional initiatives as ‘pioneer sites’. These pioneer sites are able to experiment with (new) interventions which are focused on the regional population. They all aim to restructure health services based on the concept of population management (PM). Although an unambiguous and widely accepted definition of PM is lacking, PM initiatives focus on addressing health needs at all points along the continuum of health and well-being for a specified population by integrating services across health care, prevention, social care and welfare [13]. Additionally, these pioneer sites follow the abovementioned ‘Triple Aim’ principle [6, 7]. A considerable number of the interventions implemented in the pioneer site regions are focussing on substitution of care. Substitution of care can be defined as the continual regrouping of resources across and within care settings to exploit the best and least costly solution in the face of changing needs and demands [14]. All pioneer sites will be monitored over the coming years.

This paper concerns a practice-based study focused on a cardiology primary care plus centre which is implemented in one of the appointed pioneer sites. The pioneer site, named ‘My Care’, as well as the intervention, is located in the southern part of the Netherlands [19]. In the Netherlands, all residents are mandated to purchase insurance policies, which cover an essential-benefits package. The majority of the Dutch hospitals are not-for-profit organizations and virtually all specialists are hospital-based. GPs act as gatekeepers of the health-care system and promote consistency and coordination of individual care [15–17]. All residents are registered with a GP and have unlimited access to the GP. Hospital and specialist care is only accessible through GP referral, with the exception of emergency care. In addition, when a patient with a particular complaint is referred by a GP to hospital-based specialist care, the specialist can refer the patient, for that particular complaint, to another specialist [16, 17]. It is also important to mention the influence of the different payment systems for Dutch health-care professionals. On the one hand, the GP payment system is a blended model that combines a capitated fee per enrollee with a relatively small fee for service payment per visit [15]. This blended GP payment system does not incentivize GPs to maximize the volume of care and does not encourage GPs to refer patients to specialist care. On the other hand, the payment system of the hospitals is based on a Diagnostic Related Groups (DRGs)-type system. Specialist fees are integrated into DRGs. Hospitals, and self-employed specialists, receive a payment for each DRG. This payment system incentivizes specialists to increase the volume of hospital care by increasing the number of cases, i.e. DRGs [15, 18].

The practice-based study focuses on a cardiology Primary Care Plus (PC+) centre. In this pioneer site PC+ implies substitution of specialist care in the hospital setting with specialist care in the primary care setting and it is designed for patients with non-acute and low-complexity related health complaints. Since virtually all specialists are hospital-based in the Netherlands, PC+ is a new form of health care. In the cardiology PC+ centre cardiologists provide consultations in the primary care setting. During the PC+ consultation the patients receive a comprehensive screening and afterwards the cardiologist sends his recommendations for further treatment (if needed) to the GP. For example, the specialist informs the GP about whether a referral to hospital care is needed. Based on the recommendation, the GP discusses the options for further treatment with the patient. Moreover, within PC+ the GP remains clinically in charge of the patient. PC+ strengthens the gatekeeping and coordinating role of the GP by intensifying the collaboration and communication between the specialists and the GPs. The PC+ intervention aims to improve the health of the population and patients’ experience of care and to reduce the number of referrals to hospital care (as well as hospital-based outpatient specialist care) in order to reduce health-care costs growth. In this study, the PC+ intervention is compared to care-as-usual, both are described in detail in the methods section. This paper describes the design of the evaluation of the cardiology PC+ intervention, combining qualitative and quantitative methods.

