### Care-as-usual: hospital-based outpatient cardiology care

Hospital-based outpatient cardiology care is considered care-as-usual. All GPs are allowed to refer non-acute and low-complexity patients with cardiology-related complaints to the hospital-based outpatient cardiology care. These patients receive the same care as within the PC+ centre, i.e. the same diagnostic tests carried out by health-care professionals with the same level of expertise. After the tests the patient meets the cardiologist, the cardiologist explains the results and they discuss further treatment (if needed). This underlines a significant difference with the intervention: in the PC+ centre the cardiologist provides only a recommendation on further treatment and the GP discusses the options for further treatment (instead of the cardiologist), i.e. within PC+ the GP remains in charge. The flow of patients is illustrated in Fig. 1.

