#### Health insurance claims data

This study will only focus on the health-care costs of patients, which will be measured using the health insurance claims data of the participants, which are available at Vektis. Vektis is a national information centre for all the health insurance companies in the Netherlands. The centre collects all data on the health-care utilization and health-care costs of all Dutch residents [26]. Health insurance claims data will be used to examine whether the health-care costs of an intervention patient (PC+) is different to the health-care costs of a control patient. To compare the health-care costs of an intervention patient with that of a control patient, the health insurance claims of each patient participating in the intervention or control group will be used, with a focus on GP care, PC+ and hospital care. Moreover, it has been decided to take into account the health-care costs per participant over a period of 6 months. The starting point is the date of referral to the PC+ centre (intervention group) or the hospital-based outpatient cardiology care (control group).

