#### Health-care costs

Health-care costs will be measured using health insurance claims data. This study will not cover all related health-care costs but will only focus on health-care costs (including patients’ compulsory deductible). Out-of-pocket payments and indirect costs made from a societal perspective (e.g. labour market, informal care) will not be included. The health-care costs per participant is measured over a period of 6 months after the consultation at the PC+ centre or the hospital-based outpatient cardiology care. This concerns data regarding health-care costs on primary care, PC+, hospital care and diagnostics.

Efficiency of care means, according to the IOM, avoiding waste, particularly waste of equipment, supplies, ideas and energy [19]. With regard to this research, it will be measured whether the number of consultations of patients, hospital admissions and referrals will decrease after the implementation of PC+, which is related to efficient use of equipment and health-care professionals and time of patients. Efficiency of care will be measured using data from the cardiology PC+ centre, the hospital and Vektis. The data will consist of the following items: 1) the average number of consultations at the hospital of a patient over a period of 6 months; 2) the average number of hospital admissions of a patient over a period of 6 months; and 3) the number and percentage of patients that are referred to hospital care after PC+.

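### The efficiency outcome counts consultations at the hospital only, so contacts that PC+ moves to the centre or the GP drop out of it; lower claims need not mean lower resource use either

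*Protocol article*

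**What the plan says.** **Efficiency.** The Health-care costs part of Outcome parameters ties efficiency to whether patients' consultations, hospital admissions and referrals fall, and links this to the use of equipment, professionals and patients' time. It then lists three items. The first is "the average number of consultations at the hospital of a patient over a period of 6 months"; the others are hospital admissions and referral to hospital after PC+. Table 1 labels the consultation row without naming a setting, and its footnote gives the PC+ centre, the hospital and Vektis as sources.

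**Costs.** Costs are "measured using the health insurance claims data of the participants, which are available at Vektis". They cover primary care, PC+, hospital care and diagnostics over 6 months. The compulsory deductible is included; out-of-pocket and indirect costs are not.

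**Payment rules.** The Background describes GP payment as "a blended model that combines a capitated fee per enrollee with a relatively small fee for service payment per visit". On the hospital side, "Hospitals, and self-employed specialists, receive a payment for each DRG", and the specialist's fee is part of that payment.

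**What PC+ moves.** The section on the intervention places the tests and the cardiologist's consultation at the PC+ centre and lets low-complexity care stay in primary care. The care-as-usual section gives the main contrast between the groups: in PC+, "the cardiologist provides only a recommendation on further treatment and the GP discusses the options for further treatment (instead of the cardiologist".

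**The concern.** The stated question is about consultations of patients; the listed measure is about consultations in one building. PC+ exists to move contacts out of that building. A measure limited to it will record the move itself as a gain, whether or not professionals and patients spend less time overall.

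The cost outcome has a related but weaker problem. Work taken over by the GP enters a patient's claims only as the visit fee, whereas a hospital case enters as a full DRG payment. A fall in claims can therefore partly reflect payment rules rather than use of resources.

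The Objectives section expects less waste and lower costs, and the Discussion offers the results as guidance for expanding PC+ and for other regions. With the listed measures, the study could not separate a real saving in care from care shifted to settings that are not counted or are paid differently.

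**Working it through.** The article gives no tariff, GP fee, capitation share, contact count or onward-referral rate, so there is no stated figure to reproduce. The structure can still be worked through; every numerical value below is an assumption.

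**1. Consultations.** Per patient over 6 months, let
- h = hospital consultations of a control patient;
- q = share of PC+ patients referred on to hospital, with k hospital consultations each;
- g = GP contacts of a PC+ patient minus those of a control patient;
- 1 = the PC+ consultation, which every attending PC+ patient has by design.

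Difference, PC+ minus control:
- listed measure (hospital only): qk − h
- all settings: 1 + qk + g − h
- gap between the two: 1 + g

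The gap depends on neither h, q nor k. The 1 follows from the design; g is unknown.

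Examples with q = 0.2, k = 1, g = 1:
- h = 1: hospital only 0.2 − 1 = −0.8; all settings 1 + 0.2 + 1 − 1 = +1.2. The listed measure shows a reduction while total contacts rise.
- h = 3: hospital only 0.2 − 3 = −2.8; all settings 1 + 0.2 + 1 − 3 = −0.8. Both fall, but the listed measure overstates the fall by 2 contacts.

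The hospital-only count can thus agree or disagree in sign with the total, and the planned item cannot show which.

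**2. Claims.** Set the hospital DRG payment at 100. Let P be the PC+ price, g the extra GP visits, f the GP fee per visit and c the resource cost of a visit. Capitation is paid for enrolled patients in both groups and cancels.
- claims difference = P + 100q + gf − 100
- difference with GP work at resource cost = P + 100q + gc − 100
- GP work missing from claims = g(c − f)

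With f = 3 throughout:

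| P | q | g | c | Claims difference | With GP work at c | Missing |
|---|---|---|---|---|---|---|
| 40 | 0.1 | 1 | 10 | −47 | −40 | 7 |
| 60 | 0.2 | 3 | 15 | −11 | +25 | 36 |
| 60 | 0.4 | 1 | 10 | +3 | +10 | 7 |
| 100 | 0.6 | 3 | 15 | +69 | +105 | 36 |

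Row 2 in full: 60 + 20 + 9 − 100 = −11, against 60 + 20 + 45 − 100 = +25.

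Two things follow. If the visit fee is below the cost of the visit and g is positive, the GP component is under-recorded in PC+, and this can reverse the sign. The claims difference itself can go either way, from −47 to +69 over these assumptions. The table also takes the DRG payment and the PC+ price as equal to their resource costs, which the article does not show.

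**The case against.** The strongest reply is that claims are the right measure for a question about spending. The article declares that scope, and an extra GP visit really does add only its fee to expenditure. The article also sets out both payment systems openly, and costing detail is commonly left to fuller documents. This stands for the cost outcome: claims are not a measurement error, and the issue arises only when a lower total is read as lower resource use or greater efficiency.

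A reader might go further and infer that PC+ must come out cheaper whatever happens. The documents do not support that:
- PC+ is costed as its own item, the tests and the cardiologist's consultation stay with the centre, and patients referred on add hospital claims.
- GPs being paid chiefly by capitation is an inference; no share is given.
- Nothing says that every PC+ patient has a separate paid GP visit, or that controls have none, so g could be small.
- DRG and PC+ prices may also depart from resource cost in unknown directions, so the net distortion across all prices has no established sign.

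The reply does not reach the efficiency item. There the mismatch lies within one section of the article, between the question posed and the count listed. The third item, referral to hospital after PC+, does not repair it, because it too counts nothing outside the hospital.

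**Conclusion.** The point holds for the efficiency outcome and, in a limited form, for costs.

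**Efficiency:** the hospital-only count favours PC+ by 1 + g contacts per patient relative to a count over all settings. The 1 rests on the design; g needs data. The direction holds unless PC+ patients have at least one GP contact fewer than controls, which is unlikely when the treatment discussion moves to the GP.

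**Costs:** the claims total is a valid measure of insurer payments. It records GP work only through the visit fee, so it need not track resource use. The size of that effect cannot be obtained from the article: 7 to 36 units per 100 of DRG payment is an illustration, not an estimate. Whether PC+ is cheaper or dearer on claims remains an open empirical question.

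**What to change.** 1. In the Health-care costs section and Table 1, replace or supplement hospital consultations with consultations per patient over 6 months in both groups, reported by setting (hospital, PC+ centre, GP) and in total. The sources are already named: PC+ centre records, hospital records and Vektis claims, which include GP care.
2. State that the cost outcome takes the insurer-payment perspective. Report a lower claims total as lower insurer payments, and call it an efficiency gain only if total contacts, GP contacts included, support that.
3. Optionally, add a unit-price analysis. If done, it should use resource-based unit prices for GP, PC+ and hospital care alike; repricing GP contacts alone would mix perspectives and tilt the comparison against PC+.

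The cost is some wording and slightly more data extraction, assuming that GP claims can be obtained at visit level, which the article does not confirm. The efficiency result may turn out less favourable to PC+.

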### Objectives and underlying premises of PC+

This overall study aims to evaluate the effects of cardiology PC+ centre on the Triple Aim outcomes. The underlying premises of the researchers on the effects of the intervention are that the cardiology PC+ centre will result in an (at least) equivalent health of the population, improved quality of care as experienced by patients and a reduced number of referrals to hospital-based outpatient cardiology care, and hence reduced health-care costs.

The underlying premises are grounded on several hypotheses. Firstly, it is supposed that the health of the study population (patients with non-acute and low-complexity cardiology complaints) will be at least the same, since the patients receive the same diagnostic tests and the care is provided by health-care professionals with the same level of expertise. Thus, the cardiology PC+ centre and hospital-based outpatient cardiology care will lead to the same health outcomes. After the introduction of PC+, the patients who need more specialized hospital care are likely to be referred by their GP to the hospital and the patients who do not need hospital care will remain in primary care.

Secondly, the aim of the introduction of PC+ is to improve patients’ experience of care. In this study the component patients’ experience of care is based upon the six dimensions of health-care performance of the Institute of Medicine (IOM), which partially overlaps with the last premise about health-care costs [19]. It is supposed that PC+ will improve: 1) the effectiveness of care since PC+ will result in fewer unnecessary referrals to hospital-based outpatient cardiology care, thus less overuse of care, 2) the timeliness of care since PC+ will decrease the waiting time, 3) the patient-centredness of care since an underlying rationale of PC+ is being respectful and responsive to individual patient preferences, needs and values, and 4) the efficiency of care since PC+ will result in less waste of expensive hospital-based outpatient cardiology care. Efficiency of care is related to health-care costs, therefore it will be included in this dimension. In addition, it is supposed that PC+ has no effect on the level of 5) safety of care and 6) equity of care and thus it is supposed that these will remain at the same level.

Finally, it is supposed that the introduction of PC+ will lead to reduced health-care costs by: 1) fewer referrals to hospital-based outpatient care because of the introduction of PC+, 2) lower costs in PC+ than in hospital-based outpatient care, due to lower overhead costs (i.e. the same cardiology screening will costs less in PC+), 3) less use of additional hospital-based services because it is supposed that a significant number of the patients referred to PC+ will not be referred to hospital care afterwards, but will remain in the primary care setting, and 4) GPs will gain more knowledge because of the enhanced collaboration and communication with the cardiologists. Hence, in the long term, it is possible that they will refer fewer patients, to either PC+ or hospital-outpatient care, for a cardiology screening and instead treat the patients themselves.

## Methods

This clinical observational study will adhere to the SPIRIT guidelines. The SPIRIT checklist will be used and it is added as supplementary [see Additional file 1]. The following paragraphs will describe the intervention versus care-as-usual, the study design and the methods of this research.

### The pioneer site

The ‘My Care’ region is a geographically demarcated region, located in the most southern part of the Netherlands. It consists of 11 municipalities, 277,000 residents, approximately 135 GPs and one hospital. The region is characterized by a relatively unhealthy population with a low socio-economic status (SES) as compared to the overall population of the Netherlands [20]. Moreover, it has the highest percentage of patients with a chronic disease in the Netherlands, namely 68.5% [20]. This results in a relatively high demand for health care and thereby high health-care expenditures, especially for chronic care, diagnostics and medication [21, 22].

The pioneer site ‘My Care’ is a partnership between the care group called ‘General Practitioners Eastern South-Limburg’, which is a legal entity of all GPs in the region (in Dutch: Huisartsen Oostelijk Zuid-Limburg) [23], the regional hospital Zuyderland Medical Centre, the patient representative foundation called ‘House for Care’ (in Dutch: Huis voor de Zorg) and the dominant health insurance company in the region (named: CZ*)*.

